## Abstract

**Background:**

Hand dermatitis can be a serious health problem in healthcare workers. While a range of skin care strategies and policy directives have been developed in recent years to minimise the risk, their effectiveness and cost-effectiveness remain unclear. Evidence now suggests that psychological theory can facilitate behaviour change with respect to improved hand care practices. Therefore, we will test the hypothesis that a behavioural change intervention to improve hand care, based on the Theory of Planned Behaviour and implementation intentions, coupled with provision of hand moisturisers, can produce a clinically useful reduction in the occurrence of hand dermatitis, when compared to standard care, among nurses working in the UK National Health Service (NHS) who are particularly at risk. Secondary aims will be to assess impacts on participants’ beliefs and behaviour regarding hand care. In addition, we will assess the cost-effectiveness of the intervention in comparison with normal care.

**Methods/Design:**

We will conduct a cluster randomised controlled trial at 35 NHS hospital trusts/health boards/universities, focussing on student nurses with a previous history of atopic disease or hand eczema and on nurses in intensive care units.

Nurses at ‘intervention-light’ sites will be managed according to what would currently be regarded as best practice, with provision of an advice leaflet about optimal hand care to prevent hand dermatitis and encouragement to contact their occupational health (OH) department early if hand dermatitis occurs. Nurses at ‘intervention-plus’ sites will additionally receive a behavioural change programme (BCP) with on-going active reinforcement of its messages, and enhanced provision of moisturising cream.

The impact of the interventions will be compared using information collected by questionnaires and through standardised photographs of the hands and wrists, collected at baseline and after 12 months follow-up. In addition, we will assemble relevant economic data for an analysis of costs and benefits, and collect information from various sources to evaluate processes.

Statistical analysis will be by multi-level regression modelling to allow for clustering by site, and will compare the prevalence of outcome measures at follow-up after adjustment for values at baseline. The principal outcome measure will be the prevalence of visible hand dermatitis as assessed by the study dermatologists. In addition, several secondary outcome measures will be assessed.

**Discussion:**

This trial will assess the clinical and cost effectiveness of an intervention to prevent hand dermatitis in nurses in the United Kigdom.

**Trial registration:**

ISRCTN53303171: date of registration, 21 June 2013.

## Background

Occupational irritant hand dermatitis is a major risk in healthcare. In a recent study, the 1-year prevalence of self-reported hand dermatitis among healthcare workers in a Dutch university medical hospital was 24 %, as compared with less than 10 % in the general population [1]. Amongst healthcare workers, nurses are the group at highest risk of hand dermatitis, with an estimated point prevalence of 18–30 % [2, 3]. Moreover, in a study of German geriatric nurses, two thirds of those who reported hand dermatitis stated that it had developed after they had joined the profession [2]. Consistent with this, among Korean nursing students, the prevalence of hand dermatitis increased from 7 % in the first year to 23 % in the fourth year of training [4]. The costs of hand dermatitis to the individual and employer are high. It not only affects quality of life, but also can lead to loss of employment [5, 6]. Once an individual has developed irritant hand dermatitis the prognosis is poor. In a 15-year follow-up study of a Swedish general population sample, about a third of those with hand dermatitis needed on-going medical treatment and 5 % experienced long periods of sickness absence, loss or change of job, or ill-health retirement [7]. Affected individuals may also experience negative psychosocial consequences, such as sleep disturbance and interference with leisure activities [7].

The high prevalence of hand dermatitis in nurses is attributed to frequent hand-washing and poor hand-drying techniques [8]. Current hand-cleansing policies in the UK National Health Service (NHS) are driven by efforts to reduce bacterial colonisation and transmission of infections, and the emphasis is on frequent use of hand rubs before and after patient contact, and washing with soap and water if the hands are visibly soiled [8]. However, little attention is paid to prevention of hand dermatitis.

For a nurse who develops irritant hand dermatitis, the condition is likely to be aggravated by exposure to hand hygiene measures. The presence of hand dermatitis may discourage nurses from undertaking adequate hand decontamination due to discomfort or concern about exacerbating skin lesions. It is known that 50 % of people with hand dermatitis are colonised with *Staphylococcus aureus* [9], and although controversial, there is a theoretical risk that nurses with hand dermatitis infected by methicillin-resistant *Staphylococcus aureus* (MRSA) could transmit the infection to patients. Occupational health (OH) professionals often have to advise nurses with active dermatitis to refrain from work until the lesions are healed, as it is difficult for them to avoid frequent hand-washing unless they are redeployed to a non-clinical area.

Various measures might help to prevent hand dermatitis in nurses and reduce the problems that it causes.

### Moisturisers

Two systematic reviews of the management of occupational dermatitis [10, 11] have concluded that moisturisers contributed importantly to both prevention and treatment at work. A review by the former Occupational Health Clinical Effectiveness Unit at the Royal College of Physicians focussed on the evidence for managing established occupational dermatitis, as distinct from prevention [10]. It found inconsistent evidence from two studies in which moisturisers had been used as part of a complex intervention in nurses [12, 13], but concluded that there was sufficient evidence to recommend that skin care programmes should include the use of emollients.

Guidelines produced by the British Occupational Health Research Foundation [11] recommended that the regular application of emollients helps to prevent the development of occupational dermatitis, citing three high-quality studies [14–16]. One randomised control trial (RCT) found an improvement in all outcomes, including clinical skin inspection. In the other, transepidermal water loss (TEWL) improved among construction workers who used pre- and after-work creams compared to controls, but there was no difference in clinically assessed skin condition [15]. Moisturisers also improved skin condition in workers with damaged skin [17]. More recent reviews have also concluded that there is some evidence to support the use of educational interventions that include moisturisers, but this came from a small number of workplace studies, and the authors strongly recommended that further large high-quality RCTs in working groups were needed [18, 19].

In the experience of the dermatologists and OH physicians in our research team, moisturisers are not widely used by healthcare workers in the UK. This anecdotal observation is supported by a study of nurses working in intensive care units (ICUs) in Germany which found that only 15 % of the 204 respondents reported that they applied moisturising creams after hand- washing and only 2 % after skin disinfection with hand rubs. Furthermore, 9 % never applied skin care to their hands and 72 % reported that they did not perform final skin care after the last hand-wash of the day [20].

### Hand cleansing

The use of antibacterial hand rub with the addition of moisturisers for hand hygiene reduces the drying and cracking of the skin that commonly results from repeated hand cleansing with soap and water [21]. In addition, antibacterial hand rubs are associated with increased hand hygiene compliance and reduced rates of nosocomial infection [22].

### Hand-drying and glove use

Proper drying of the hands after washing is pivotal to good hand hygiene and care, particularly as wet skin is more likely to facilitate the transmission of bacteria than dry skin. A recent review of hand-drying processes [23], which included 12 studies, concluded that paper towels are superior to electric air dryers and, therefore, should be recommended in locations where hygiene is vital, such as clinical environments. This was supported by guidelines from the World Health Organization [8].

Skin care programmes that incorporate measures of the type that have been described have shown a beneficial effect in the prevention of hand dermatitis in healthcare workers [12, 13, 24, 25]. However, a recent systematic review suggested that educational programmes could benefit from being more strongly informed by psychological theory, since their success relies on employees adopting appropriate preventive and protective behaviours [18]. Psychological theory has proved useful in understanding the behavioural determinants of hand hygiene practices among healthcare professionals [8, 26] and so is likely to also be useful in the design of interventions to modify such practices. Moreover, a meta-analysis of Internet-based behavioural change interventions found that more extensive use of theory was associated with significantly greater effects and, in particular, that Internet interventions based on the Theory of Planned Behaviour (TPB) tended to have more substantial effects on behaviour [27]. One of the few studies applying psychological theory to the prevention of occupational hand dermatitis examined the TPB’s ability to predict the behaviour of a sample of German patients with occupational hand dermatitis receiving an inpatient tertiary prevention programme. The TPB variables explained 30 % of the variance in post-intervention dermatitis prevention behaviour and 38 % of the variance in intentions for preventive behaviours [28]. Systematic review of relevant evidence shows that forming implementation intentions and specific plans about how, when and where health-promoting behaviours will be performed increases the likelihood of individuals acting on their positive intentions [29]. Furthermore, evidence suggests that reminding individuals of their implementation intentions can facilitate longer-term changes in behaviour [30, 31].

Although there are good reasons to expect that well-designed skin care programmes would be beneficial for nurses, their effectiveness and cost-effectiveness remain uncertain. Trials to date have been limited by size and the possibility that the control group was aware of the intervention [32], or by a failure to address cost-effectiveness [33]. There is a need for a pragmatic trial to evaluate the clinical and cost-effectiveness of a behavioural change programme (BCP) to improve the compliance of nurses with measures to prevent occupational hand dermatitis.

## Aims and objectives

We will test the hypothesis that a bespoke, web-based behavioural change intervention to improve hand care, coupled with provision of hand moisturisers, can produce a clinically useful reduction in the prevalence of objectively assessed hand dermatitis after 1 year, when compared to standard care, among nurses working in the National Health Service (NHS) who are particularly at riskSecondary aims will be to assess impacts on participants’ beliefs and behaviour regarding hand care (as a measure of adherence), days off sick over a 1-year follow-up period, and use of hand moisturisersIn addition, we will assess the cost-effectiveness of the intervention compared with normal care

## Method/Design

### Concise statement of proposed research

We will conduct a cluster RCT of an intervention to improve hand care at 35 sites (12 NHS acute hospital trusts/health boards which provide OH care to both student and ICU nurses, 18 NHS trusts which provide OH care to ICU nurses and 5 university OH departments which provide OH care to student nurses). We will focus on two groups of staff: (1) student nurses who are about to start their first clinical placements, and who are at increased risk of hand dermatitis because of a past history of atopic disease or hand eczema; and (2) nurses working in ICUs, who are at increased risk of hand dermatitis because of the nature of their work.

Ethics approval to conduct the trial has been granted by the National Research Ethics Service (NRES) Committee London − City Road and Hampstead (REC reference: 13/LO/0981). Ethical approval applies to all research sites taking part in the study. Trial registration: ISRCTN number 53303171: date of registration, 21 June 2013.

### Design and theoretical/conceptual framework

The study will be a cluster RCT with sites as the unit of randomisation. Sites will be randomly allocated to be ‘intervention-light’ or ‘intervention-plus’. Study group 1 will be student nurses who are about to start their first clinical placements, and who are at increased risk of hand dermatitis because of a past history of atopic disease or hand eczema. Study group 2 will be nurses working in ICUs who are at increased risk of hand dermatitis because of the nature of their work. All participants are required to provide written consent at the time of recruitment into the study.

### Intervention-plus

The intervention-plus in both staff groups will centre on a bespoke online behavioural change package (BCP) which will include advice: on when and when not to use gloves; on when to use antibacterial hand rubs; on when to use moisturising cream; and to contact OH early if hand dermatitis occurs.

The BCP has been developed by members of the study team with expertise in dermatology, occupational medicine, nursing, and health psychology. Care has been taken to ensure compatibility with current guidance on infection control. We have emphasised WHO recommendations that hands should only be washed with soap and water if visibly soiled. At all other times, hands should be cleansed with antibacterial hand rubs [8].

To maximise the probability of participants following best practice, they will be asked to form implementation intentions for performing each of the behaviours in their workplace. A record of each participant’s implementation intentions will be generated by the online BCP programme and emailed to them. In the event of a participant being unable to access the online BCP, they will be posted a paper-based magazine version of the BCP which will reflect the information provided in the online BCP. Participants will asked to read through the material provided and write down their action plans in spaces provided. They will then be asked to keep the paper-based BCP in a convenient place so that they can refer back to it as required.

The BCP will be supported by provision of facilities to encourage adherence. These will include personal supplies of moisturising cream for at-risk student nurses, and provision of (1) optimal equipment for cleaning hands, and (2) moisturising cream dispensers on ICUs.

The BCP will be made available to ICU nurses once they have undergone baseline assessment (see below), and to student nurses 2 weeks before they start their first clinical attachment. It will be actively reinforced over the course of the study by consistent messages on skin care from the local OH and control of infection teams, and from local line management. Research has shown that senior role models have important effects on more junior healthcare workers’ hand hygiene behaviours [34, 35], and it seems reasonable to assume that this influence will extend to behaviours that prevent dermatitis. To facilitate this, when implementing intervention-plus, we will engage in a dialogue with local OH staff and line managers about the nature and purpose of the study and will provide them with information on the advice which will be given in the BCP, to ensure that they promote consistent messages on skin care. The SCIN research team will also write to any NHS sites at which student nurses undertake clinical placements, but which are not themselves participating study sites, to ensure they are informed about the study.

We will offer the BCP online to allow nurses to access it at a time convenient to their schedules, to permit standardisation of the delivery of key information across all intervention- plus sites, and to reduce the potential burden on OH staff. Moreover, if the BCP is found to be effective in this trial, it will be simple to scale up access to the website in order to deliver the BCP across the country.

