### Comparator (intervention-light)

Nurses at intervention-light sites will be managed according to what would currently be regarded as best practice, with provision of an advice leaflet about optimal hand care entitled ‘Dermatitis: occupational aspects of management. Evidence-based guidance for employees’ (also provided to the intervention-plus group) and encouragement to contact their OH department early if hand dermatitis occurs. However, they will not receive the BCP or active reinforcement of its messages. Nor will they routinely be offered supplies of moisturising cream over and above what is already standard practice at their site.

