
If the intervention is shown to be cost-effective then we will make estimates of the number of nurses who might access the intervention were it to become recommended practice. This will in turn allow us to estimate the budget impact for the NHS and the benefits in terms of total QALYs gained. Uncertainty around these estimates will be investigated through the sensitivity analyses describe above.

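### The trial tests the intervention-plus package, but one sentence words the result as the BCP's alone, and the economic analysis costs only part of that package

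*Protocol article*

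**What the plan says.** The protocol article describes two arms: "Sites will be randomly allocated to be ‘intervention-light’ or ‘intervention-plus". Under Intervention-plus, the online BCP is accompanied by "personal supplies of moisturising cream for at-risk student nurses" and by "provision of (1) optimal equipment for cleaning hands, and (2) moisturising cream dispensers on ICUs". The same section adds reinforcement by occupational health (OH), infection control and line management: "It will be actively reinforced over the course of the study by consistent messages on skin care". Of the nurses at intervention-light sites, the Comparator section says: "However, they will not receive the BCP or active reinforcement of its messages". They keep whatever cream is standard at their site, and both arms receive the advice leaflet and are encouraged to see OH early.

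The Abstract and the Aims and objectives section state the hypothesis for the behavioural intervention together with moisturiser provision. Method of analysis compares intervention-plus with intervention-light. The paragraph in Intervention-plus on why the BCP is delivered online then says "if the BCP is found to be effective in this trial, it will be simple to scale up access to the website".

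The Economic analysis section bases the cost of the BCP on the time taken to develop it and the staff time taken to use it. Cream supply is counted under healthcare costs. If the intervention proves cost-effective, "we will make estimates of the number of nurses who might access the intervention were it to become recommended practice", and these estimates lead to an NHS budget impact and a total of QALYs gained.

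**The concern.** The scale-up sentence states a condition about one component, while the trial compares bundles. A reader of a positive trial could take it as evidence that website access alone would reproduce the result.

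By itself that would be a matter of wording. It matters more because the economic section uses a similarly narrow view of what the intervention is. The benefits would come from everything delivered at intervention-plus sites, while the listed costs cover the BCP and the cream. Incremental cost-effectiveness ratios (ICERs), acceptability curves and the budget impact would then set the benefit of the whole package against part of its cost. An adopter could plan for too small a budget, or see the intervention called dominant when it is not.

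**Working it through.** **Step 1. What differs between the arms, and what is costed.** Sources are the Intervention-plus, Comparator and Economic analysis sections.

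| Component | Intervention-plus | Intervention-light | Cost item listed |
|---|---|---|---|
| Leaflet, encouragement to see OH early | yes | yes | common to both arms |
| Online BCP | yes | no | development and access time |
| Extra cream | personal supplies (students); dispensers (ICUs) | site standard only | cream, under healthcare costs; dispensers not listed |
| Active reinforcement | yes | no | staff time not listed |
| Hand-cleaning equipment | ICUs | not mentioned | not listed |

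Three things differ by design for students (BCP, cream, reinforcement) and four for ICU nurses (equipment as well).

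**Step 2. What the contrast identifies.** Each study group has one randomised contrast. With k components, each present or absent, there are 2^k possible combinations: 2^3 = 8 for students and 2^4 = 16 for ICU nurses. The trial observes two of them, all and none. The difference is the joint effect, including any interaction. The effect of the BCP without the others is not estimated.

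**Step 3. Whether another planned analysis separates them.** The mediation test in Method of analysis has prevention behaviours as its outcome and beliefs and plans as mediators. It does not concern dermatitis or the components. Process evaluation describes access to and completion of the BCP. Outcome measures include moisturiser use, but no analysis by component is planned. None of these yields a BCP-only effect on dermatitis.

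**Step 4. Consequence for the ICER.** The protocol defines the ICER as the difference in costs divided by the difference in outcomes. Let U be the unlisted cost per nurse at intervention-plus sites (equipment, dispensers, reinforcement time) and ΔE the package effect:

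- ICER for the package as delivered = (ΔC listed + U) / ΔE
- ICER from the listed items = ΔC listed / ΔE
- Understatement = U / ΔE

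The article gives no value for U, so the result is shown per £1. ΔE comes from the three planning scenarios under Sample size, which are not predictions:

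- 24 % to 10 %: ΔE = 0.14, and 1/0.14 = £7.14
- 24 % to 12 %: ΔE = 0.12, and 1/0.12 = £8.33
- 24 % to 14 %: ΔE = 0.10, and 1/0.10 = £10.00

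Each £1 per nurse left out thus lowers the cost per additional dermatitis-free participant by about £7 to £10. For N nurses, the budget impact is short by N × U.

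**Step 5. Whether the sensitivity analyses cover this.** Development and access time are varied by 10–50 % in either direction. If these listed items total B per nurse, the range reaches at most 1.5B, which would contain the full cost only if U is no more than 0.5B. The article gives neither figure, and the variation is not aimed at omitted items. The budget-impact uncertainty relies on the same analyses.

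**The case against.** The strongest reply is that the scale-up sentence is not the trial's inference. It ends a paragraph on why the BCP is online and remarks that web delivery is easy to extend. It does not say that cream, equipment or reinforcement would be dropped. Wherever the inference is formally fixed, it concerns the package. This largely stands: hypothesis, design and primary analysis need no change, and the wording fault is confined to that sentence.

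On costs, cream is included, and the budget-impact text speaks of the intervention, never of the website. That also stands: a reader might infer a website-only budget impact, but the verb access is too little to show it. What remains is that the article says what intervention cost is based on, and that basis leaves out equipment, dispensers and reinforcement time. A fuller economic plan may list them; if so, the article's description should match it.

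Three other inferences go too far:

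- **Cream could fully explain any effect.** The Moisturisers section favours emollients overall, but it reports inconsistent results in nurses and one trial without a difference in clinically assessed skin condition. When to use cream is also part of the BCP's advice, so supply and advice are meant to act together.
- **Some percentage of the effect belongs to the BCP.** A range from nothing to everything only restates that the share is not identified.
- **The Background misstates the aim.** Its call to "evaluate the clinical and cost-effectiveness of a behavioural change programme" gives the motive for a trial and draws no conclusion from one.

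**Conclusion.** The point holds in a limited form. The trial can validly show whether the intervention-plus package reduces hand dermatitis. It cannot show that the BCP, or access to its website, does so alone, and the scale-up sentence should not imply that it can.

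The consequence that could change a reported result is economic: the effects and QALYs are those of the package, while the listed costs omit ICU equipment, dispensers and reinforcement time. The bias is U/ΔE in the ICER and N × U in the budget impact, both making the intervention look cheaper. Its absolute size cannot be given because the documents do not state U. This rests on two assumptions: that the unlisted items have a cost above zero, and that the article's account of the cost basis is what will be applied.

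A reader might infer that the design is faulty or that a further arm is required. The documents do not support this: a pragmatic package trial is legitimate, and the stated hypothesis is of that kind.

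**What to change.** 1. In the scale-up sentence under Intervention-plus, make the condition that the intervention-plus package is effective, and add that the trial does not estimate the effect of the website alone.
2. In Economic analysis, define intervention cost for the package as delivered in each study group: BCP development and access time, cream, ICU equipment and dispensers, and the OH, infection-control and line-management time spent on reinforcement. Include the added items in the sensitivity analyses.
3. Define the NHS budget impact and total QALYs for roll-out of that same package.

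The cost is a little more costing work, mainly a record of equipment and reinforcement time at intervention-plus sites, and a less favourable claim for the website. The Background sentence, design, sample size and primary analysis stay as they are.
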